##### Acceptability

The acceptability of NMS Assist will be assessed during qualitative interviews with a subset of the people with Parkinson disease, care partners, and HCPs. These semistructured interviews will enable participants to provide more in-depth feedback about what they liked about NMS Assist and any barriers or frustrations they experienced using the system. The theoretical framework of acceptability will be used to structure the questions asked about acceptability in the semistructured interview guide because it considers several different facets of acceptability before, during, and after the intervention delivery [11]. Perceived acceptability at these different time points is likely to have an impact on the adoption and sustained engagement with NMS Assist.

##### Engagement

System use data will be collected to gather data about participants’ engagement with the NMS Assist system. However, system use data only captures one component of engagement and is not a valid measure of engagement on its own [33,34]. Engagement has cognitive, behavioral, and affective aspects [34-37], and engagement with a digital health intervention includes engagement with the system itself, with various components of the intervention, and with the health behaviors it is trying to support. Therefore, system use data will be supplemented with semistructured interviews and a user engagement questionnaire (eg, the eHealth Engagement Scale [38] or the User Engagement Scale [39]) to gain a better understanding of user experience engaging with the intervention and the recommended behaviors.

##### Costs

A cost analysis impact of implementing the NMS Assist system will be conducted. Resource use (time spent on the system) and costs to implement throughout the 12-month intervention period to be compared to published data on costs for the standard of care.

### Study Duration and Follow-up

The study will consist of 3 main phases over 24 months: preparation (6 months), delivery of the intervention (12 months, see Figure 1 for follow-up data collection points), and analysis and dissemination (6 months). The study team will monitor the use of NMS Assist and assure the system is being used within designed parameters during the study. No incentives will be provided to encourage adherence; the study is assessing the use of NMS Assist in the real world, and we expect that the benefits for people with Parkinson disease and care partners provided by the monitoring and self-help features will sufficiently encourage adherence to the study.

### Data Collection

The evaluation shall follow the NASSS framework [10] that aims to help predict and evaluate the impact of digitally enabled health programs (see Table 1).

**Table 1 table1:** Description of quantitative and qualitative data collection strategies structured using the nonadoption, abandonment and challenges to the scale-up, spread, and sustainability framework [10].

NASSS^a^ domain and participants		Quantitative data	Qualitative data (topics in SSI^b^)
**Illness or condition**			
	All	Participant characteristics (eg, age, sex, cognitive impairment, depression, digital literacy)	Appropriateness of the system for individual context
	People with Parkinson disease and care partners	Disease characteristics	—^c^
**Technology**			
	All	Usability	Usability (barriers and facilitators to use)
	All	—	Perceptions of system features, data privacy, and security
	HCP^d^	System use data	Perceptions of the data provided by the system and use of data to improve understanding or inform care decisions
	People with Parkinson disease and care partners	System use data	Perceptions of self-management resources and system feedback
**Value proposition**			
	All	—	Motivation to participate in the study
	All	—	Suggestions for system improvement
	People with Parkinson disease and care partners	Care partner quality of life	Perceptions of impact of system on confidence, knowledge, and skills for managing nonmotor symptoms.
	People with Parkinson disease and care partners	Nonmotor symptoms and their burden	Perceptions of impact of system on symptom burden
	People with Parkinson disease and care partners	Patient functioning and well-being	Perceptions of impact of system on quality of life
	People with Parkinson disease and care partners	Patient’s knowledge, confidence, and skills (patient activation) at managing their health care	—
	—	Costs and time commitments will be evaluated as part of the cost assessment using quality of life data collected in the study and published data on existing care treatment costs	—
**Adopter system**			
	All	—	Acceptability
	All	—	Barriers and facilitators to adoption
	HCP	Characteristics of high and low system users	Reasons for high or low engagement with system
	People with Parkinson disease and care partners	Proportion who completed questionnaires and frequency of completion	Effort required to learn and use the system
	People with Parkinson disease and care partners	Proportion who accessed the self-help resources relevant to their specific symptoms (as reported on the NMSQ^e^)	Perceived impact of system on care partner burden
**Organization**			
	HCP	System use data (eg, number of log-ins per user, time spent on system, number of notifications responded to or actioned)	Issues reported with implementing the system in care practices
	HCP	—	Perceptions of impact of system on routine care processes, workflows, and workloads
**Wider context**			
	—	Implications for the national standards of care and inclusion in preexisting care pathways will be investigated	—
**Embedding and adaptation over time**			
	All	Participant retention throughout the study period	Reasons for continued/discontinued use of system during study
	All	System use data (engagement) throughout study period	Perspectives on continued use and adaptations of the system in future
	—	Costs and time commitments will be evaluated as part of the cost assessment using quality of life data collected in the study and published data on existing care treatment costs	—

^a^NASSS: nonadoption, abandonment and challenges to the scale-up, spread, and sustainability.

^b^SSI: semistructured interview.

^c^Not applicable.

^d^HCP: health care professional.

^e^NMSQ: Nonmotor Symptoms Questionnaire.

#### Quantitative Data Collection

The primary outcome, patient and care partner activation, will be completed at the beginning of the intervention period and monthly thereafter to measure the impact of NMS Assist on the knowledge, confidence, and skills of people with Parkinson disease and care partners over time [17] (see Figure 1). People with Parkinson disease and care partner scores on the NMSQ, PDQ-8, and PDQ-C will be recorded automatically by the system. The proportion of people with Parkinson disease who are contacted by their nurse or clinician based on their symptom questionnaire responses will be measured. Quantitative app and portal use data will be captured by the system to examine patterns of engagement with the questionnaires, self-help resources, and triggered health care contacts. Data about participant characteristics, recruitment, and retention will also be recorded.

Participants will also be asked to attend 3 study visits, at baseline, 6 months, and 12 months (see Figure 1), where they will complete the long-form PDQ-39 [19] and the Warwick-Edinburgh Mental Wellbeing Scale (WEMWBS) [21] and will have administered the Movement Disorder Society–Nonmotor Rating Scale (MDS-NMS) [18] and the EQ-5D-5L [20].

#### Qualitative Data Collection

Qualitative data will be collected at 4 time points: baseline, 3, 6, and 12 months (see Figure 1). Purposive sampling will identify 20 participants, including people with Parkinson disease (with various demographic and disease characteristics), care partners, and HCPs, for qualitative semistructured interviews. The interviews will assess the system’s acceptability structured using the theoretical framework of acceptability [11]. They will also explore participant motivation to participate, their engagement with the system, and any barriers or facilitators to use, usability issues, or technical difficulties they encounter. The perceived impact of the system on the knowledge, confidence, skills, and symptom burden of people with Parkinson disease and care partners will also be investigated to triangulate with the quantitative measures.

### Data Analysis

The primary analysis will be the comparison of mean Patient Activation Measure scores [17] at each month. A repeated measures analysis of variance will be conducted to identify any significant changes in mean Patient Activation Measure scores over the 13 time points (baseline and monthly until 12-months postbaseline). If the normality assumption for a repeated measures analysis of variance is not met, a nonparametric alternative will be used.

The same analysis for the primary outcome will be conducted for the health and well-being outcome measures and the System Usability Scale, comparing the measure scores at the baseline, midpoint, and end points. Exploratory analyses will be conducted to identify potential associations between demographic or disease characteristics and outcome measures to inform hypotheses for future evaluations. All other quantitative data will be analyzed using descriptive statistics.

Semistructured interviews will be coded by 2 investigators using thematic analysis [40]. Triangulation of the quantitative questionnaire, system use, and qualitative semistructured interview data will be conducted to validate findings.

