### Sample Size

We will recruit 60 people with Parkinson disease–care partner dyads and their associated HCPs—the exact number of HCPs cannot be determined until the people with Parkinson disease–care partner dyads have been recruited, as we will include HCPs who are associated with those patients. Of the 60 dyads, at least 20 people with Parkinson disease–care partner dyads will be purposively sampled for a semistructured interview. We will also be inviting the HCPs associated with those dyads to separate semistructured interviews.

Since this is a feasibility study, a formal sample size calculation has not been performed. A sample size of 60 people with Parkinson disease–care partner dyads was selected because this is an achievable number of patients to recruit within the study period based on our prior research.

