#### Recruitment

Participant eligibility will be determined by the screening process they undergo in outpatient care at the University Hospitals Plymouth NHS Trust. All eligible participants will be invited to participate with no influence from the researchers. Interview participants will also be randomly selected (from demographic groups) by a computer script of intervention users. All participants will be included in the process evaluation’s quantitative analyses, thus avoiding recruitment bias.

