#### Sensitivity

The outcomes measures that concern potentially sensitive topics (personal health and well-being) will be delivered to the patients’ phones via the app or by their HCP in a standard clinical setting. This enables them to avoid discussing any sensitive topics with a researcher. The semistructured interview questions will focus only on the participants’ experiences with the app (engagement and acceptability) and are intended to avoid any areas of cultural or psychological sensitivity.

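### A 13-point repeated measures ANOVA with only a normality safeguard is a poor primary method for monthly Patient Activation Measure scores that will probably have gaps

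*Protocol article*

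**What the plan says.** The Data Analysis section names the primary test: "A repeated measures analysis of variance will be conducted to identify any significant changes in mean Patient Activation Measure scores". The scores run from baseline to month 12, which makes 13 per person. The section gives one contingency: "If the normality assumption for a repeated measures analysis of variance is not met, a nonparametric alternative will be used". The same analysis is to be applied to the health and well-being measures and the System Usability Scale at three time points.

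Other sections bear on whether a full set of 13 scores is realistic:

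- Sample Size: "We will recruit 60 people with Parkinson disease", as dyads with a care partner. The number rests on achievability, with no power calculation.
- Study Duration and Follow-up: "No incentives will be provided to encourage adherence".
- Table 1 treats retention, reasons for stopping use, and the proportion and frequency of questionnaire completion as things to be studied.
- Safety Considerations lists users' unwillingness to take the system into routine use as a key risk.

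The Conclusions of the Abstract make a favourable observed effect on patient activation one of the success criteria. The Primary Outcome section says the study does not measure efficacy, and Strengths and Limitations concedes that there is no group comparison.

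**The concern.** Two features of the named method fit this design badly.

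**Missing scores.** A standard repeated measures ANOVA works on complete rows, so one missed month out of 13 removes the person. The Friedman test, the usual rank-based replacement, has the same requirement, so the stated switch would not help. The protocol itself foresees that some people will stop using the system. If those people also have lower activation, the remaining rows over-represent people who are doing well. In a single-arm study nothing offsets that selection: it appears directly as change from baseline.

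**Sphericity.** With 13 monthly scores, neighbouring months will usually correlate more strongly than distant ones. The uncorrected F test then rejects too often. The plan guards against non-normality, which is the lesser threat here.

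At stake is a decision to move to larger trials that rests partly on a gain produced by who stayed in the analysis, or on a p-value that is too small.

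**Working it through.** The protocol gives no power calculation, alpha, SD, missing rate or covariance, so there is no figure of its own to reproduce. The checks below use n = 60 (Sample Size, one person with Parkinson disease per dyad) and 13 time points (Data Analysis). Everything else is an assumption and is labelled as such.

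**1. People with all 13 scores.** Assume baseline is always present and each of the 12 later months is missed independently with probability m. Complete rows = 60 × (1 − m)^12.

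| m per month | (1 − m)^12 | Complete rows of 60 |
|---|---|---|
| 1% | 0.886 | 53.2 |
| 2% | 0.785 | 47.1 |
| 5% | 0.540 | 32.4 |
| 10% | 0.282 | 16.9 |

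If 20% drop out by month 12 and the rest miss 5% of months, 60 × 0.80 × 0.540 = 25.9 remain. With dropout alone of 10%, 20% or 30%, 54, 48 or 42 remain. Gaps clustered within the same people leave more complete rows than the table shows at the same monthly rate.

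**2. Type I error.** Simulated with no true change, n = 60, 4,000 runs per setting and an assumed alpha of 0.05. The Monte Carlo standard error near 0.05 is √(0.05 × 0.95 / 4000) = 0.003. Epsilon is the sphericity index, with 1 meaning that sphericity holds.

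| Assumed covariance | Epsilon | ANOVA, uncorrected | Greenhouse-Geisser | Friedman |
|---|---|---|---|---|
| Compound symmetry | 1.00 | 0.051 | 0.039 | 0.046 |
| Random intercept and slope (smaller slope variance) | 0.91 | 0.059 | 0.041 | 0.056 |
| Random intercept and slope (larger slope variance) | 0.75 | 0.066 | 0.040 | 0.056 |
| AR(1), rho 0.5 | 0.67 | 0.081 | 0.044 | 0.076 |
| AR(1), rho 0.7 | 0.45 | 0.103 | 0.042 | 0.084 |
| AR(1), rho 0.9 | 0.27 | 0.139 | 0.048 | 0.107 |

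With 3 time points and AR(1) rho 0.7, the uncorrected rate is 0.051. The sphericity problem therefore belongs to the 13-point analysis and not to the three-visit outcomes.

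**3. Apparent change among completers.** Simulated with a true mean change of zero and 3,000 runs of 60 people. Assumed true-score SD at baseline is 0.8, SD of individual 12-month change 0.6 and measurement error SD 0.5, so the observed baseline SD is √(0.64 + 0.25) = 0.94. The chance of returning a score either ignores current activation or rises with it.

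| Return of scores | Average monthly missing | Mean completers | Apparent 12-month change |
|---|---|---|---|
| Unrelated to activation | 5.0% | 32.4 | 0.00 |
| Rises with activation | 4.8% | 35.4 | 0.07 |
| Rises with activation | 9.1% | 23.3 | 0.12 |

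The last two are 0.073 / 0.94 = 0.08 and 0.124 / 0.94 = 0.13 observed baseline SDs.

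A harsher set of assumptions lets dropout depend on the change observed so far, with 27% to 44% lost by month 12. Completers then gain 0.12 to 0.39 SD, against 0.00 to 0.02 SD for a likelihood-type analysis of all scores with the covariance taken as known. That mechanism is missing at random by construction, so it shows the remedy at its best. No mixed model was fitted under the mechanism in the table.

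**The case against.** The strongest reply is that this is a condensed article. It does not say that incomplete rows are dropped, and it does not rule out a sphericity correction; both may be settled in a full protocol or analysis plan that is not shown. That stands as far as it goes: the complete-row requirement and the uncorrected F test are inferred from the standard form of the named method. But the article does name that method for 13 time points, and a later correction to the degrees of freedom would not bring back lost participants.

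It is also fair that every size above depends on assumed inputs. At 1% missing per month the loss is small. Bias is zero if missingness is unrelated to activation. Type I error is 0.05 under compound symmetry, and the highest rates need strong serial correlation. The study disclaims efficacy, and its success criterion is an observed effect alongside feasibility, usability, acceptability and safety, not a significant F test.

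Two stronger readings are tempting, and the document does not support them.

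- A reader might see a contradiction with the Recruitment section under Ethical Considerations, which speaks of "quantitative analyses, thus avoiding recruitment bias". That sentence is limited to the process evaluation and follows the text on choosing interviewees. It does not define the analysis set for the primary outcome.
- A reader might infer that anyone who abandons the app loses the primary outcome, because the Sensitivity section mentions "phones via the app or by their HCP in a standard clinical setting" and the visit list does not name the Patient Activation Measure. But the Sensitivity sentence covers only measures on sensitive topics. The measure is not among the questionnaires listed as app-based, and the Usability section shows that online or paper surveys are also in use. Figure 1, which carries the schedule, is not shown. The delivery route is simply not stated.

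**Conclusion.** The point holds as a mismatch between method and design. A 13-point repeated measures ANOVA whose only stated safeguard concerns normality is a poor choice for monthly scores in an unincentivised digital study where disengagement is foreseen.

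The size is conditional:

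- **Lost participants:** from about 7 of 60 at 1% independent monthly missingness (60 − 53) to about 43 of 60 at 10% (60 − 17), if the method is applied in its standard form.
- **Spurious gain:** about 0.08 to 0.13 observed baseline SDs in the moderate scenarios, larger under stronger outcome-dependent dropout, and none if missingness is unrelated to activation.
- **Type I error:** about 0.06 to 0.14 if sphericity fails and nothing is corrected, otherwise about 0.05 or slightly below.

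Lost participants and selection are the weightier part, because a correction to the F test leaves them untouched. It should be fixed, since the result feeds a success criterion in a study without a control arm. The feasibility aim keeps it from being more serious than that.

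**What to change.** Replace the ANOVA and its normality switch with a prespecified linear mixed model on all available Patient Activation Measure scores:

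- month as a categorical fixed effect;
- a named structured covariance, such as random intercept and slope or heterogeneous AR(1), since an unstructured 13 × 13 matrix has 13 × 14 / 2 = 91 parameters;
- small-sample degrees of freedom, such as Kenward-Roger;
- the 12-month change reported with its confidence interval, because an omnibus test over 13 means has no direction.

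Using the same model for the three-visit outcomes is optional. The reason there would be missing data, not sphericity.

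State that the measure at months 6 and 12 is collected at the existing clinic visits whether or not the participant still uses the app.

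The cost is a change of wording and, if it is not already planned, one questionnaire at two visits that already take place. The downside is that the model assumes scores are missing at random, which may not hold exactly if non-return depends on unobserved current activation. Clinic collection at months 6 and 12 would make the assumption more credible. The covariance must also be chosen in advance.

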### Ethical Considerations

#### Ethics Approval

Ethical approval is being sought from the Health Research Authority and the relevant Research Ethics Committee [41]. The study is registered at ClinicalTrials.gov [NCT05414071].

#### Confidentiality, Data Management, and Consent

The NMS Assist system will store identifiable data as part of the clinical record. The solution is in compliance with the UK Data Protection Act 2018 [42]. Each participant will be given a unique identifier with the key stored securely for reference purposes. Only the researchers will have access to research data and only the HCPs will have access to their patients’ clinical data. Interview recordings will be anonymized and destroyed following transcription. After having the opportunity to review the participant information sheet, which explains the study procedures and provides clear information (reviewed by the people with Parkinson disease and care partner coapplicants) about confidentiality, data privacy, and security and participant rights, participants will be asked to provide explicit consent for specific aspects of the study and data management.

#### Recruitment

Participant eligibility will be determined by the screening process they undergo in outpatient care at the University Hospitals Plymouth NHS Trust. All eligible participants will be invited to participate with no influence from the researchers. Interview participants will also be randomly selected (from demographic groups) by a computer script of intervention users. All participants will be included in the process evaluation’s quantitative analyses, thus avoiding recruitment bias.

#### Power Relations and Other Potential Biases

Preestablished inclusion and exclusion criteria will be used to avoid any potential bias from the researchers as well as any coercion from participants. To prevent participation bias, only participants who would not otherwise progress down the standard care pathway will be excluded.

#### Sensitivity

The outcomes measures that concern potentially sensitive topics (personal health and well-being) will be delivered to the patients’ phones via the app or by their HCP in a standard clinical setting. This enables them to avoid discussing any sensitive topics with a researcher. The semistructured interview questions will focus only on the participants’ experiences with the app (engagement and acceptability) and are intended to avoid any areas of cultural or psychological sensitivity.

#### Timing

To mitigate any time concerns for participants, qualitative interviews will last for a maximum of 60 minutes. If this is a concern for any of the people with Parkinson disease, the interviews can take place over 2 sessions.

